### Intervention

#### CBM interventions

Each training task, both in the active and placebo version, consists of four blocks: a brief practice block, a brief assessment block, and two active or placebo training blocks. The assessment block serves the purpose of measuring the strength of the bias at the start of every session and tracking any progressive change in the cognitive bias as a result of the CBM training.

In each task, each trial starts with a fixation cross in the centre of the screen for a duration randomly drawn from a uniform distribution ranging between 500 ms and 1000 ms. This setting is designed to keep participants’ attention focused and to avoid anticipatory responses. Whenever a wrong response is given, a red cross appears on the screen to allow for correction. The inter-trial interval is 500 ms. Both active and placebo training modules present a total of 2016 training trials divided into 6 sessions (336 training trials per session).

Stimuli presented in the assessment and training tasks are tailored to participants’ choice of gambling categories. At baseline, participants are asked to choose two gambling activities they feel are or could be the most problematic out of five categories (roulette and dies, slot machines, card games, sport betting, and Belgian bingo). Multiple random samples of stimuli for the two selected gambling activities and respective control pictures will then be presented in all tasks. Practice blocks present neutral stimuli (grey geometrical pictures) to practice the task instructions.

#### Attentional bias training

Attentional bias is assessed and trained through an adapted version of the Visual Probe Task (VPT) [31, 36, 44]. The VPT is a computerized speeded reaction-time task in which participants are asked to respond to probes located in two different positions on the computer screen. During the task, a gambling-related picture and a control picture are presented next to each other on the screen for 500 ms. After the stimuli presentation, a small arrow (8.3% of the width/height of the picture) pointing upwards or downwards is presented for 750 ms in either of two trial formats: it replaces one of the two pictures (*after* format) – measuring speeded detection of gambling-related stimuli – or is positioned on top of one of the pictures (*on top* format) – measuring the relative difficulty to disengage from gambling-related stimuli. Assessment trials in the training sessions are presented in a between-session alternating block design, with trials for each format presented in separate blocks in separate sessions; whereas the two trial formats are intermixed in the training blocks. Participants are instructed to respond as fast as possible to the direction of the arrow, by pressing the corresponding key on the keyboard (U and N). The response window is set to 4000 ms. In case of no response the trial is restarted after repeating the task instructions.

The assessment version of the task is composed of three blocks: one practice block and two test blocks, one per trial format, presented in counterbalanced order across participants. The arrow is presented on the gambling picture (gambling trials) and the control picture (non-gambling trials) equally often. Attentional bias is computed by subtracting the median response time (RT) for correct responses on gambling trials from the median RT for correct responses on non-gambling trials, separately for the two trial formats. In the training version of the task, participants in the active condition are trained to direct their attention away from gambling cues and towards neutral cues by exposing them only to non-gambling trials, whereas participants in the placebo condition are presented with 50% gambling and 50% non-gambling trials (as in the assessment version).

Stimuli are pairs of matched gambling and non-gambling pictures, which are counterbalanced with a 2 × 2 design in assessment and placebo training blocks (stimulus position on the screen: left or right; arrow location: on the gambling or on the non-gambling picture) and counterbalanced only for stimulus position in active training blocks. Probe direction is set randomly upwards or downwards with the restriction that up and down appears equally often.

#### Approach bias training

Automatic approach tendencies towards gambling are assessed and trained with the modified Approach-Avoidance Task (AAT), including a zooming feature [32, 34, 35, 44, 52]. The AAT is a computerized speeded reaction-time task in which participants are asked to react to the stimulus presentation format and ignore the stimulus content.

In this task, a gambling-related picture or a control picture is presented at the centre of the screen. The picture is tilted five degrees to the left or to the right. Participants are instructed to respond to the tilt direction of the picture by pushing pictures tilted to the left away and pulling pictures tilted to the right closer. The combination of tilt direction and response (left/push and right/pull versus left/pull and right/push) is counterbalanced across participants. In order to perceptually mimic the approach/avoidance effect, a zooming effect progressively decreases the picture size upon a push response, whereas it increases it upon a pull response. The average zooming duration is 750 ms; the stimulus stays on screen for 3000 ms; in the case of no response the trial is re-started after repeating the task instructions.

The assessment version of the task is composed of three blocks: one practice block and two test blocks. Gambling and control pictures are presented equally often in both push and pull formats. Approach bias scores are computed by subtracting median RTs for correct responses to pull and push trials for each stimulus category: (gambling/push – gambling/pull) and (control/push – control/pull). For each stimulus category, a positive score indicates relatively faster RTs for approach responses compared to avoidance, whereas a negative score indicates relatively faster RTs for avoidance responses compared to approach. In the active training version, participants are trained to avoid gambling cues by exposing them only to gambling/push and control/pull trials, whereas in the placebo version both stimulus categories are presented equally often in both formats (as in the assessment version). The stimuli are pairs of matched gambling and non-gambling pictures, which are counterbalanced for presentation format only in the assessment version.

#### Task stimuli

An ad-hoc large stimulus set was purposely created by adapting existing stimulus development guidelines for cognitive bias research to the context of gambling [53] and according to previous studies assessing gambling cue reactivity [6]. Stimuli are 40 pairs of matched pictures (500 × 500 pixels) of gambling cues and controls for each of five gambling categories: roulettes and dies, slot machines, card games, sport betting, and Belgian bingo (applicable to Belgian participants only). Pictures include common gambling games present in both the Netherlands and Belgium.

All gambling pictures were photographed in real-life gambling settings (i.e., casinos, betting rooms, and slot machine halls) with a high-resolution camera, by consistently using the same framing and shooting angle (i.e., from the front) and without using flash. Control pictures have been similarly developed and are as similar as possible in complexity and pictorial features (i.e., colour, luminosity, and shooting angle) to gambling pictures. Gambling and control pictures were matched for complexity and comparability as follows [6]: equal number of overview and detail pictures and screenshots of websites when the gambling category also included online gambling sites (i.e., sport betting, slot machines, card games, and roulette and dies). Control pictures include real-life, daily objects (or websites for online stimuli) or locations completely unrelated to gambling (i.e., no reference to money or cash dispensers, no video games or anything else connected to gambling). All pictures were processed in Photoshop CS6 (Adobe Systems Incorporated, San Jose, CA, USA) to adjust for minor imperfections, size, exposure, brightness, and contrast, and to ensure maximal picture similarity.

#### Personalised motivational feedback

Although successful in reversing maladaptive cognitive biases, online CBM interventions suffer from issues that are common to online self-help tools, namely, impersonality and large dropout rates, which, among other reasons, are possibly due to the progressive decrease of users’ engagement with the online tool [42]. Hence, the main goal of adding personalised feedback is to promote participants’ retention to the intervention, by increasing their adherence to the training intervention and supporting their motivation to change their gambling behaviour.

The content and style of the feedback draws on motivational interviewing (MI) principles [54] and combines cognitive, behavioural, and motivational elements into a focused psycho-educational leaflet, which can also be downloaded. MI is a client-centred counselling approach aimed at promoting and enhancing intrinsic motivation to change by exploring participants’ motives and pros and cons of changing their behaviour, resolving any ambivalence about change, and reinforcing their self-efficacy [54]. First face-to-face brief MI-based interventions for excessive gambling behaviour have been shown to significantly reduce gambling frequency and expenditure (for a recent meta-analysis, see Yakovenko et al. [55]). A recent clinical trial tested the effectiveness of an online version of MI-based personalised feedback on gambling behaviour, related cognitive distortions and negative consequences of gambling, and found a significant reduction in gambling frequency at follow up [45]. Importantly, also a brief advice intervention incorporating minimal MI elements (i.e., personalised feedback about one’s gambling and pros and cons of gambling, change plan worksheet) proved to be beneficial [56].

In the current study, the automated personalised feedback takes the form of a summative feedback adapted from a self-help book for problem gamblers [57], elaborating participants’ responses to an ad-hoc baseline questionnaire. The questionnaire asks about participants’ expectations and motives for gambling, any experienced negative consequence of their gambling behaviour, and the reasons for changing their gambling behaviour. The feedback is given in two stages: during the baseline assessment and during the training sessions. Immediately after completing the baseline questionnaires, the first part of the feedback thoroughly explores the participants’ reported gambling motives and positive expectancies. At the start of each training session, a more concise feedback reviews the reported negative consequences of gambling and the reasons for reducing or stopping it. When the goal is not abstaining but reducing gambling, the feedback ends with a reminder of the gambling limit plan that participants scheduled when filling in the personalised feedback questionnaire (i.e., maximum amount of time and money to be spent on gambling per day in the coming 2 weeks).

The feedback generally addresses the participant in a non-judgmental, personal, and empathic style and starts at baseline with a factual summary for each gambling motive. The feedback then continues by introducing doubt about gambling-related distortions (e.g., illusion of control) and by examining their plausibility and veracity, with the goal of highlighting the discrepancy between distorted beliefs and attitudes and actual consequences of gambling behaviour. Participants are encouraged to consider the feedback in light of their personal goals and experiences and are further provided with examples of alternative sources of reward, by suggesting action-oriented strategies to increase alternative behavioural reinforcement (i.e., resuming gambling-free lifestyle, engaging in activities incompatible with gambling, and planning leisure activities) and to strengthen social reinforcement (i.e., renewal of supportive social relationships, repairing damaged relationships, and socializing with non-gamblers).

The feedback provided at the start of each training session reminds the participants of the negative consequences they experienced because of their gambling and further reviews the chosen reasons for either reducing or abstaining from gambling. The feedback highlights personal and concrete core values (e.g., healthy relationships and financial responsibility) and reinforces self-efficacy and commitment to change behaviour to achieve the desired goal (e.g., feeling better, improving relationships, and keeping a job position).

### Measures

The schedule of all forms and study procedures along the study time points is presented in Fig. 2.

**Fig. 2 Fig2:**
[figure not shown]
SPIRIT Figure: Schedule of forms and procedures per study time point

#### Baseline assessment

After registration, participants’ general socio-demographic details are collected (age, gender, highest education degree attained, personal and household monthly net income, and marital status), followed by a questionnaire asking about their habitual gambling behaviour [58]: gambling frequency in the past 12 months, in the past month and on average per month; average amount of time spent on gambling per day; average amount of money spent in the past 12 months, in the past month and on average per month; age of gambling onset (age when they gambled for the first time); any previous treatment for gambling and/or for other addictions or psychiatric disorders such as depression. Severity of gambling problems in the past 12 months (South Oaks Gambling Scale, SOGS [59]), severity of gambling addiction (itemisation of DSM-V diagnostic criteria), and preferred gambling activities are also assessed. Participants then complete the ad-hoc questionnaire about gambling motives, negative consequences, and advantages of stopping/reducing gambling.

After the personalised feedback questionnaire, participants complete a second battery of questionnaires evaluating their readiness to change their gambling behaviour (Gambling Readiness for Change Questionnaire (G-RCQ) [58]), depressive symptoms (Beck Depression Inventory-II, short version (BDI-II) [60]), substance use (CORE questionnaire short version; CORE Institute, http://core.siu.edu/surveys/index.php), and alcohol problems (Alcohol Use Disorders Identification Test (AUDIT) [61]), impulsivity (Barratt Impulsiveness Scale (BIS-11) [62]), and self-esteem (Rosenberg Self-esteem Scale (RSES) [63]).

After the questionnaires, a computerised version of the classical Stroop Task [64] is used to assess interference control capacity. In this task, participants have to classify words and symbols according to their ink colour and ignore the content. The task has been designed similar to the method used by Boffo et al. (2015) [44]. Finally, the baseline session ends with the assessment versions of the VPT and AAT, presented in counterbalanced order between participants, followed by two questions to control the quality of collected data (“While you were working on the TOP-training/your session of training, how often did things happen to distract you?”, “How much attention did you pay to the questions and/or tasks and your responses?” [65]).

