### The present study: objectives and hypotheses

Being the first CBM study in the gambling field, the primary goals of the RCT are to explore (a) whether gambling behaviour decreases over time as a result of a CBM intervention, and (b) whether the two CBM interventions would successfully decrease or reverse the targeted bias. Primary outcomes are monthly frequency and expenditure (i.e., average amount of money spent per month) [46], assessed at baseline, after the intervention, and in the medium term (after 3 and 6 months). The secondary outcomes include measures of gambling-related attentional and approach bias, administered at baseline, after the intervention, and at the 3-month follow up. Participants’ severity of gambling problems and depressive symptoms are also monitored over all time points.

An additional secondary moderated mediation analysis will explore the moderating effects of trait impulsivity and interference control capacity (i.e., cognitive inhibition), which have been considered as endophenotypical vulnerability markers for SUD and GD [47, 48]. Greater impulsivity and diminished ability to cope with cognitive interference could lead to lesser ability to ignore gambling cues in the environment and to suppress prepotent behavioural responses, and could thus moderate the strength of the cognitive biases. In line with previous results of CBM studies in alcohol addiction [21, 35], any change in cognitive bias as a result of the training intervention would mediate changes in the gambling outcome variables. Further, participants with stronger cognitive biases and/or lower interference control capacity and higher impulsivity at baseline would benefit more from a CBM intervention than participants with weaker cognitive biases and/or stronger interference control capacity and lower impulsivity.

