## Methods

### Study design

The study is a pilot, double-blind RCT with a four-group parallel design: two groups complete either the ABM training or the AppBM training and two control groups receive the placebo version of either training. The two placebo training varieties consist of a continuous assessment task without any stimulus-response contingency (i.e., participants are equally trained away from and towards both gambling and control stimuli [34, 35, 44]). The manipulation of the task stimulus-response contingency offers greater control over the comparison between experimental and placebo conditions, ruling out non-specific effects related to performing a computerised intervention, while retaining the same tasks, stimuli, and instructions. Given the absence of previous studies on the effects of CBM interventions with gamblers, the present design does not introduce a factorial combination of the two CBM interventions, since the two training interventions have never been individually tested with gamblers before, making it premature to experimentally test any interaction effect.

Participants complete a total of 10 sessions: a first baseline assessment session including the automated personalised feedback on their reported gambling motives and beliefs, six training sessions [49], a post-intervention assessment, and two follow-up assessment sessions after 3 and 6 months. Each training session starts with shortened automated personalised feedback about participants’ reported negative consequences of their gambling and advantages of reducing or quitting, after which motivation to train and craving for gambling are assessed, and proceeds with the training task (about 15 minutes). Participants can train almost daily, with a between-session interval of at least 20 hours; however, they are suggested to complete two to three sessions per week, allowing them to complete the full intervention in about 3 weeks. The total duration of the study is estimated to be about 7.5 months for each participant. The entire study, including all assessment measures, computerised tasks and automated personalised feedback, is delivered online through the LOTUS and JASMIN experiment delivery online platforms developed and managed by the University of Amsterdam.

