#### Outcome measures

Primary outcome measures are changes in the past-month gambling frequency and expenditure (i.e., money spent on gambling, irrespective of winnings) as assessed at baseline, post-intervention, and both follow-up sessions. The secondary outcome measures include changes in attentional (VPT) and approach (AAT) bias scores from baseline to the 3-month follow-up. Changes in depressive symptoms (BDI-II) and severity of gambling problems (SOGS) from baseline to the follow-up sessions are also explored, although not included as main outcomes. Intervention credibility and expectancies are also assessed with the Credibility/Expectancy Questionnaire [66] during the second session of training, to evaluate participants’ general experience with the study.

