### Data analysis

Multiple imputation of missing data will be performed for intention-to-treat analyses. Before running all analyses, all variable distributions will be screened for normality assumptions and univariate outliers. The use of parametric or non-parametric statistical tests will be adjusted accordingly. Each training group will be compared to its control group to check for any baseline difference in demographics (e.g., age and gender), severity of gambling problems (SOGS), and alcohol use. When significant differences are found and the relevant baseline variables also correlate with the outcomes of interest, they will be added as covariates in subsequent analyses.

Changes in gambling frequency and expenditure from baseline to the 6-month follow up will be examined through two separate 2 (condition: active training vs. placebo) × 4 (time: baseline, post-intervention, 3-month and 6-month follow up) mixed analysis of variance (ANOVA) analyses, one per training module. Each CBM condition is contrasted against its control condition, with the baseline assessment as reference time point for the following time points.

Changes in gambling cognitive biases as a result of each CBM intervention will be explored with a 3 (time: baseline, post-intervention, 3-month follow up) × 2 (condition: active vs. placebo training) × 2 (stimulus category: gambling vs. control) mixed ANOVA for approach bias (i.e., AAT task) and a 3 (time: baseline, post-intervention, 3-month follow up) × 2 (condition: active vs. placebo training) × 2 (trial type: on top vs. after) mixed ANOVA for attentional bias (i.e., VPT task). Any change in depression symptoms and gambling problems would be explored using two 2 (condition: active vs. placebo training) × 4 (time: baseline, post-intervention, 3-month and 6-month follow-up) mixed ANOVA analyses, one per training module.

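### The only recall window given for the SOGS is 12 months; if that form is repeated after baseline, its windows reach back before randomisation and change in gambling severity is blunted, most at the two earlier visits

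*Protocol article*

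**What the plan says.** All references are to the protocol article.

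- **Baseline assessment** lists "Severity of gambling problems in the past 12 months (South Oaks Gambling Scale, SOGS [59". This is the only place where a recall period is attached to the SOGS. The same section separates a 12-month from a past-month period for gambling frequency and money spent.
- **The present study: objectives and hypotheses** says that participants' "severity of gambling problems and depressive symptoms are also monitored over all time points".
- **Outcome measures** says that changes in depressive symptoms and "severity of gambling problems (SOGS) from baseline to the follow-up sessions are also explored, although not included as main outcomes". The primary outcomes there, frequency and expenditure, refer to the past month.
- **Data analysis** says: "Any change in depression symptoms and gambling problems would be explored using two 2 (condition: active vs. placebo training) × 4" levels of time, namely baseline, post-intervention, 3 months and 6 months, with one analysis per training module.
- **Study design** suggests a session rate "allowing them to complete the full intervention in about 3 weeks", followed by a post-intervention assessment and "two follow-up assessment sessions after 3 and 6 months". It puts total participation at about 7.5 months.

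No recall period is given for the SOGS after baseline. The schedule of forms (Fig. 2) is not reproduced in the text available.

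**The concern.** A repeated measure can show change only over the time it asks about. No planned visit comes as late as 12 months after baseline. A 12-month question asked at any later visit therefore still covers time before randomisation. By randomisation, that earlier time is the same on average in the active and placebo arms, and training cannot undo what happened in it. It adds a shared component to every later score, which pulls the condition-by-time effect towards zero.

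What is at stake is a secondary reading of the trial. The SOGS is the gambling-severity scale that the plan names for a change analysis, and the study is meant to generate hypotheses for later trials. A flat SOGS profile could be taken as a sign that training leaves gambling problems unchanged when the instrument had little room to register a change.

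**Working it through.** The document states no figure for this overlap, so there is none to reproduce. The check is direct arithmetic.

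**Inputs**
- Recall window W = 12 months (Baseline assessment). Its use at later visits is assumed.
- Training length: about 3 weeks (Study design). A month is 365.25/12 = 30.44 days, so 21/30.44 = 0.69 month.
- Follow-up visits at 3 and 6 months (Study design). The text does not say whether these are counted from baseline or from post-intervention, so both are shown.
- Total participation of about 7.5 months (Study design), used as the latest possible time of the last visit.

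**Formula.** With t months from baseline to the visit, the share of the window before baseline is (W − t)/W.

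| Visit | t (months) | Share before baseline |
|---|---|---|
| Post-intervention | 0.69 | (12 − 0.69)/12 = 94% |
| 3 months, from post-intervention | 3.69 | (12 − 3.69)/12 = 69% |
| 3 months, from baseline | 3 | (12 − 3)/12 = 75% |
| 6 months, from baseline | 6 | (12 − 6)/12 = 50% |
| 6 months, from post-intervention | 6.69 | (12 − 6.69)/12 = 44% |
| Last visit at 7.5 months | 7.5 | (12 − 7.5)/12 = 37.5% |

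The Abstract gives a different schedule, with follow-up at 1 and 3 months. Counted from post-intervention, the shares would then be (12 − 1.69)/12 = 86% and (12 − 3.69)/12 = 69%.

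**What the shares mean.** The part of the window in which the arms can differ is the complement: about 6% at post-intervention, 25-31% at 3 months and 50-62.5% at 6 months. These are shares of time. They are not limits on how far the score can fall, because the document gives no item wording or scoring for the SOGS.

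**The same check on a past-month window.** At post-intervention, (1 − 0.69)/1 = 31% of the window would lie before baseline. At 3 and 6 months the overlap would be zero.

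**The case against.** **The follow-up window is inferred.** The 12-month wording appears only in the baseline section, the article is condensed, and the schedule figure is not available. This stands, and the finding is conditional on it. Repeating the same form is still the natural reading when a named scale is re-used without qualification.

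**A shorter window might be used later.** A reader might infer that the SOGS analysis then fails as well, because scores would drop through the shorter recall alone. The planned analysis does not support that. A change of window shared by both randomised arms goes into the time main effect and does not by itself create or hide a condition-by-time effect. Only the raw change from baseline within an arm would mix recall length with recovery.

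**The last visit is much less affected.** A reader might infer that most of the window lies before baseline at every visit, or that the score can hardly fall. At 6 months the share is 37.5-50%, so neither follows. How far a score could fall depends on item scoring that the document does not give. If items count any occurrence within the window, the roughly 5.3 months remaining before baseline (12 − 6.69) could still keep many items endorsed, but that scoring rule is an assumption.

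**The measure is exploratory.** Outcome measures sets SOGS change apart from the main outcomes, and Data analysis calls the whole study explorative. This stands and limits the consequence. It does not remove the point, because a recall period is fixed when data are collected and no later analysis can recover a short-window severity that was never asked.

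**Conclusion.** The concern holds in a limited form. The plan names one SOGS recall window, 12 months, and re-uses the scale for change at visits from about 3 weeks to about 7 months after baseline. If the form is unchanged, about 94% of the window at post-intervention, 69-75% at 3 months and 37.5-50% at 6 months precedes baseline. That dilutes the active-placebo difference severely at the first of these visits, substantially at the second and partly at the third.

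This rests on two assumptions: that the 12-month form is repeated at follow-up, and that training takes about 3 weeks. A reader might also infer that the trial's main conclusions are at risk. They are not on this account: the primary outcomes use a past-month window at all four time points.

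**What to change.** 1. State the SOGS recall period at every visit.
2. For the change analysis, ask the severity items with one short window, worded identically at baseline and at each follow-up. The past month would match the primary outcomes. Run the 2 × 4 analysis on that version and note that about 31% of its window at the 3-week visit still lies before baseline.
3. Keep the 12-month form at baseline to describe severity.
4. For participants assessed only with the 12-month form, do not interpret the post-intervention and 3-month SOGS contrasts as change or as absence of effect. Report the 6-month value as partly overlapping with the time before baseline.

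**Cost.** The change is one of wording in an online questionnaire, plus a short amendment. The short-window version departs from the 12-month form. Trial status says that recruitment has run since February 2015, so participants already enrolled would lack a matching baseline and the two versions could not be pooled as one change score. If the switch is judged too late, items 1 and 4 can be done alone and need no new data.
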